### Eligibility and Withdrawal Criteria

The consolidated criteria for patient enrollment are those: (1) aged 18 years or older; (2) eligible for receiving ECMO (VV or VA) therapy; (3) with mechanical ventilation; (4) with stable condition and eligible for cardiopulmonary rehabilitation after 72 h of ECMO; (5) with no contraindications for cardiopulmonary rehabilitation; (6) not pregnant; (7) with a life expectancy of more than 3 days; (8) wean from ECMO therapy within the first 3 days before the initiation of the CaRe-ECMO program; (9) not use ECMO as a bridge to recovery or definitive treatment (e.g., lung transplantation or heart transplantation); (10) not enrolled in another trial previously; and (11) sign informed consent form by the guardian (18). According to previously published guidelines, the specific indications and contraindications for VV-ECMO and VA-ECMO are given in Tables 2, 3, respectively (19, 20).

**Table 2 T2:** Indications and contraindications for VV-ECMO.

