#### Secondary Outcomes

Secondary outcomes are listed and elaborated as follows:

1) Rate of ECMO weaning will be calculated according to date of ECMO weaning fulfilled.2) Total length of ready for ECMO weaning refers to exact length in day till patients fulfill all the criteria of ready for ECMO weaning according to daily checkout records (14).3) Total length of ECMO weaning refers to exact length in day for patients treated with ECMO therapy (29).4) Rate of mechanical ventilation weaning will be calculated according to date of mechanical ventilation weaning fulfilled. Daily screening of mechanical ventilation weaning will be strictly performed with checklist shown in Table 7 according to the American Thoracic Society and the American College of Chest Physicians Clinical Practice Guideline (30).5) Total length of mechanical ventilation refers to exact length in day for patients treated with mechanical ventilation.6) All-cause mortality is defined as rate of death due to any causes and will be calculated according to date of death (31).7) Rate of major post-ECMO complications refers to rate of complications occurred after ECMO including but not limited to ECMO-related complications (e.g., thromboembolism), mechanical ventilation-related complications (e.g., pneumonia), newly developed myocardial infarction, acute kidney injury, neurologic events (e.g., stroke, seizures), and multiple organ failure (32). Information of major post-ECMO complications will be collected in the Complication Recording Sheet (Table 8).8) Diaphragmatic thickness and mobility refer to ultrasound-guided evaluation of diaphragmatic thickness and mobility under M-mode (33).9) Extracorporeal membrane oxygenation unit LOS accounts for length in day for stay of patients in the ICU unit.10) Total hospital LOS accounts for total hospital LOS in day for stay of patients in both the ECMO unit and other departments.11) Total cost for hospitalization will be calculated by addition of the cost of all the units and department admission.12) Cerebral performance category will be recorded, for those successfully weaning of ECMO, to reflect post-ECMO neurological status (34).13) Activities of daily living will be evaluated, for those successfully weaning of ECMO, with Katz Index (35).14) Health-related quality of life will be measured, for those successfully weaning of ECMO, with SF-12 (36).

**Table 7 T7:** Mechanical ventilation weaning checklist.

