Baseline demographics and clinical characteristics, directly from the medical files at randomization, will also be collected including but not limited to the following information: age, gender, main diagnosis, comorbidities (diabetes mellitus, hypertension, respiratory infection, or others), the Acute Physiology and Chronic Health Evaluation II (APACHE II) score, ECMO mode (VV-ECMO or VA-ECMO), length in hour since mechanical ventilation, partial pressure of arterial oxygen/fraction of inspired oxygen (PaO_2_/FiO_2_) in mm Hg, positive end-expiratory pressure (PEEP), tidal volume in ml/kg of predicted body weight, respiratory rate in breaths/min, plateau pressure in cm of water, driving pressure in cm of water, arterial blood pH, PaO_2_ in mm Hg, partial pressure of arterial carbon dioxide (PaCO_2_) in mm Hg, N-terminal pro-B-type natriuretic peptide (NT-proBNP) in pg/ml, creatine kinase-MB (CK-MB) in ng/l, cardiac troponin T (cTnT) in ng/l, and ejection fraction (EF) in percentage. The above data will be recorded in the Baseline Data Collection Sheet (Table 10). Apart from that, daily clinical monitoring for both the condition and ECMO running status of patient will be performed. The detailed information will be recorded in the Daily Monitoring Sheet (Table 11).

**Table 10 T10:** Baseline data collection sheet.

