**Running status of ECMO**					
Indication	□ Cardiac □ Pulmonary □ ECPR				
ECMO type	□ VA-ECMO □ VV-ECMO □ Other______				
ECMO cannulation sites	VV-ECMO: □ No □ Yes (If yes, then fill the following items) □ Right femoral vein □ Left femoral vein □ Right internal jugular vein □ Left internal jugular vein □ Other______ VA-ECMO: □ No □ Yes (If yes, then fill the following items) □ Right femoral vein □ Left femoral vein □ Right internal jugular vein □ Left internal jugular vein □ Right femoral artery □ Left femoral artery □ Other______				
Distal collateral circulation	□ No □ Yes				
ECMO flow	ECMO blood flow______L/min ECMO gas flow______L/min ECMO FiO_2_______%				
Length from ECMO response to operation	______mins				
Length of ECMO operation	______mins				
Length of MV before ECMO	______days ______hours ______mins				

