### Statistical Methods

The demographic and clinical characteristics collected at randomization will be presented as means with SDs or medians with interquartile ranges for continuous variables and as percentages for categorical variables, as appropriate.

For all the outcomes, we will estimate differences in effect size between the groups on both the intention-to-treat (ITT) and per protocol (PP) basis (39). Categorical variables will be compared with the chi-square or Fisher's exact tests and continuous variables will be compared with the Student's *t*-test or the Wilcoxon signed-rank test, as appropriate. The time effect of day the time-to-event outcomes identified (e.g., rate of ready for ECMO weaning, rate of ECMO weaning, rate of mechanical ventilation weaning, all-cause mortality, and rate of major post-ECMO complications) between the groups will be estimated with the Cox proportional hazards regression analysis and graphically illustrated using the Kaplan–Meier methods until CaRe-ECMO days 7, 14, 30, and 90, respectively (40). Variables, including total length of ready for ECMO weaning, total length of ECMO weaning, total length of mechanical ventilation, ECMO unit LOS, and total hospital LOS, will be treated with time-to-event data and will be analyzed with mixed-effects ordered logistic regression (41). Secondary outcomes with normal and non-normal distributions, including CPC, ADL, HRQoL, and diaphragmatic thickness and mobility, will be estimated for group differences with mixed-effects linear regression (41).

Considering that part of patients will definitely not reach the primary endpoint, i.e., ready for ECMO weaning at CaRe-ECMO day 7 for sensitivity purpose, we will assess the heterogeneity of the treatment effect on primary outcome and secondary outcomes in pre-specified subgroups of interest as per baseline data to be collected at randomization (e.g., age, gender, main diagnosis, comorbidities, the APACHE II score, ECMO mode, length since mechanical ventilation) by using exploratory *post-hoc* sensitivity adjusted analyses for any corresponding statistical methods mentioned above.

Interim analysis will be scheduled halfway through enrollment to check that there are no serious issues with respect to sample handling or data collection.

All the analyses will be conducted at a two-sided alpha level of 5% and will be performed using the Stata version 16 (StataCorp, College Station, Texas, USA) or other software, as appropriate.

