Additional important considerations, which we addressed when preparing the CaRe-ECMO trial protocol, were the following. First, the current trial is consisting of a RCT part followed by an open-label cohort part. According to our clinical experience and retrospective data analysis, the median length of ECMO weaning varied ~from 7 to 9 days in all the types of ECMO-supported patients. The design rationale of the RCT part is to power the primary outcome, while the following open-label cohort part is dedicated to benefit patients who do not respond to one cycle of cardiopulmonary rehabilitation. This action may impair the effects of RCT on long-term outcome observation; however, it is hypothesized to provide additional opportunity for those who are probably benefitted from active intervention (56). Second, a critical concern of the CaRe-ECMO trial design is the uncertainty of the effect size of the proposed interventions. Therefore, our attention on primary outcome selection has been shifted from the exact ECMO weaning to ready for ECMO weaning. If any significant results would be introduced in terms of earlier ready for ECMO weaning or increased rate of ready for ECMO weaning due to our proposed interventions, then it may satisfy the preliminary requirements when extending its effects to more consolidated outcomes (e.g., rate of ECMO weaning). To compensate the aforementioned risks, we introduce several evidence-based checklists to ensure the standardized definition and evaluation of ECMO or mechanical ventilation weaning (Tables 5–7) and to maximally avoid potential performance bias. Third, functional outcomes are essential to the long-term recovery; therefore, CPC index, ADL score, HRQoL score, and diaphragmatic thickness and mobility will be consecutively collected. In case when primary outcome of the CaRe-ECMO trial does not show a statistically significant difference, future trials may consider to analyze our secondary clinical and functional outcomes.

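### ECMO, ventilation and hospital lengths are defined as whole-episode totals, so variation in time before entry adds avoidable noise to these secondary outcomes, mainly ventilation and hospital stay

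*Protocol article*

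**What the plan says.** Three definitions in Secondary Outcomes are at issue.

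- Item 3, ECMO: "Total length of ECMO weaning refers to exact length in day for patients treated with ECMO therapy".
- Item 5, ventilation: "Total length of mechanical ventilation refers to exact length in day for patients treated with mechanical ventilation".
- Item 10, hospital stay: "Total hospital LOS accounts for total hospital LOS in day for stay of patients in both the ECMO unit and other departments".

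None names a start. Read plainly, each is the total for the episode.

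Eligibility and Withdrawal Criteria requires mechanical ventilation at entry and admits patients "with stable condition and eligible for cardiopulmonary rehabilitation after 72 h of ECMO". Statistical Methods says the length variables "will be treated with time-to-event data and will be analyzed with mixed-effects ordered logistic regression".

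Time already spent on the ventilator is collected. Data Collection lists "length in hour since mechanical ventilation" among the baseline characteristics, and the baseline sheet (Table 10) has a field "Length of MV before ECMO" as well as the dates of admission and of ECMO admission. Statistical Methods uses elapsed ventilation time only in exploratory post-hoc subgroup and adjusted analyses, not in the main model for the lengths.

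**The concern.** The programme can only act after entry, yet the totals also count days before it. An order-based model compares patients by their totals, so pre-entry days can reverse the order of two patients.

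Take two invented records. Patient A has 6 days of ventilation before ECMO, 3 days on ECMO before entry and 4 days after it: 6 + 3 + 4 = 13. Patient B has 0 + 3 + 8 = 11. A ranks worse, although A's time after entry is half of B's.

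Randomisation balances such differences on average, so no bias between arms arises. The price is precision: a real shortening after entry is harder to detect. These lengths are named in Trial Objectives, and the Discussion points future trials to the secondary outcomes if the primary result is not significant, so it is worth measuring them well.

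**Working it through.** **The plan's own figure.** There is none to reproduce. The 348 (366 with attrition) in Sample Size Calculation is for the primary outcome, and no power is claimed for the lengths.

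**Step 1: a constant shift.** Adding the same 3 days to every patient leaves the order of durations, the mean difference and the variance unchanged. A simulation confirms it: 183 per arm, rate ratio 1.4 after entry, exponential times, whole days, and a rank-sum test standing in for an ordered logistic model with treatment as the only covariate. Power is 77.9% with or without the 3 days when the control median after entry is 4 days, and 78.3% with or without when it is 6 days. These medians are the quoted 7 and 9 days minus 3.

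**Step 2: pre-entry time that varies.** Same model, with 3 days plus an exponential part of the stated SD. The SDs are assumed.

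| SD of pre-entry time | Median 4 d: total vs from entry | Median 6 d: total vs from entry |
|---|---|---|
| 1 d | 77% vs 80% | 77% vs 78% |
| 2 d | 71% vs 78% | 76% vs 80% |
| 4 d | 60% vs 79% | 67% vs 78% |
| 7 d | 44% vs 79% | 56% vs 79% |
| 10 d | 29% vs 78% | 47% vs 79% |

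The mean difference stays near -1.6 days (median 4) or -2.5 days (median 6) throughout. Only the noise grows. A linear model adjusted for pre-entry time holds power at 88-90% in every row.

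**Step 3: the three outcomes.** A second model assumes Weibull time after entry (shape 1.3), 25% shorter in the rehabilitation arm, with no deaths or censoring. Pre-entry time is assumed as follows:

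- ECMO: uniform 3-5 days.
- Ventilation: the same plus uniform 0-7 days.
- Hospital: uniform 3-5 days plus an exponential part with mean 7 days.

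The variance after entry in the control arm is scale² × [Γ(1 + 2/1.3) − Γ(1 + 1/1.3)²] = scale² × (1.366 − 0.853) = scale² × 0.513. That is 15.5 at scale 5.5 days and 26.6 at scale 7.2 days. The variance added before entry is:

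- ECMO: 2²/12 = 0.33, or 1-2% of the variance after entry.
- Ventilation: 2²/12 + 7²/12 = 4.42 (SD 2.1 days), or 17-28%.
- Hospital: 2²/12 + 7² = 49.3 (SD 7.0 days), or 186-318% at these short scales. At scales of 15, 20 and 30 days (variances 115, 205 and 462) it is 43%, 24% and 11%.

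Simulated rank-sum power, 183 per arm:

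| Outcome | From entry | As a total |
|---|---|---|
| ECMO length | about 87% | about 86% |
| Ventilation length | 86-87% | 74-79% |
| Hospital stay, scale 5.5-7.2 d | 86-88% | 39-52% |
| Hospital stay, scale 15, 20, 30 d | 86-88% | about 73%, 78%, 82% |

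Power follows the variance shares: almost no loss for ECMO, a moderate loss for ventilation, and for hospital stay a loss that depends on how long patients remain after entry.

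**The case against.** The case against is substantial.

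- **No start is written.** A journal article may leave the exact time origin to the full protocol, so its absence alone is no finding. That stands. The point rests on what is written: totals as the outcome, an order-based model, and elapsed ventilation time confined to exploratory analyses.
- **The 72 h itself does no harm.** A reader might infer that the 72 h dilutes the effect and costs power in all three lengths. It does not (step 1), and ECMO length is essentially unaffected. A ratio of medians would move toward 1, but the plan reports no such ratio. Nor does 72 h before entry follow strictly for ventilation, which could begin after cannulation, or for hospital stay, since Table 10 allows ECMO to be placed out of hospital.
- **The share of ECMO time is uncertain.** One might set 3 days against the Discussion's figure, "the median length of ECMO weaning varied ~from 7 to 9 days in all the types of ECMO-supported patients", and get 33-43%. That median covers all ECMO patients. Those still on ECMO after 72 h would be expected to have longer totals and so a smaller share.
- **The low hospital figures rest on one input.** They assume a stay after entry of about the length of ECMO support, although the definition includes other departments. With longer stays most of the loss goes.
- **The question is partly covered.** ECMO and ventilation weaning are analysed by Cox regression to CaRe-ECMO days 7, 14, 30 and 90, counted from programme initiation. A shortening after entry would be tested there. No such analysis is listed for hospital stay.
- **Totals are legitimate measures of burden**, alongside cost. That also stands, and they need not be dropped.

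**Conclusion.** The point holds as a minor matter of precision. As written, the length outcomes include pre-entry time, and its variation between patients adds noise that the main model does not remove. Under the assumed inputs, ventilation length loses roughly 7 to 13 points of power (86-87% to 74-79%). Hospital stay loses anything from a few points to about half its power (86-88% to 39-82%), and ECMO length about one point. The direction is secure for any pre-entry time that varies independently of time after entry. The size is not, because the article gives no SD for pre-entry time and no distribution of time after entry, and the simulations ignore death.

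The documents do not support reading this as bias between arms, as an effect of the 72 h rule itself, or as a threat to the primary outcome or its sample size.

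**What to change.** In Secondary Outcomes and Statistical Methods, do one of two things:

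1. Count the analysed length outcomes from randomisation in both arms.
2. Keep the totals and adjust the main model for pre-randomisation duration: elapsed ventilation time for ventilation length, and time since admission or since ECMO start for the hospital and ECMO lengths.

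The second option uses values fixed before allocation, so the adjustment is safe. Whole-episode totals can still be reported as measures of burden.

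The cost is about one sentence in each section. Elapsed ventilation time is already a baseline variable, and Table 10 records ventilation before ECMO and the admission and ECMO dates. No new data or patients are needed.

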**Indications for VA-ECMO (one or more of the following)**
1. Rapidly deteriorating or severe cardiogenic shock (cardiac Index < 2.2 L/min/m^2^ with ^*^ VIS > 40) with LVEF < 35%
2. Rapidly deteriorating or severe cardiogenic shock (cardiac Index < 2.2 L/min/m^2^ with ^*^ VIS > 40) with LVEF of 35–55%, and severe mitral regurgitation or aortic stenosis
3. Two consecutive lactate values ≥4 mmol/L (with at least 30 min interval between sampling), with non-decreasing trend on steady dose of inotropes and/or vasopressors
4. Witnessed cardiopulmonary resuscitation for more than 10 min or intermittent ROSC but unable to maintain

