**Contraindications for VA-ECMO**
1. Irreversible non-cardiac organ failure limiting survival (e.g., severe anoxic brain injury or metastatic cancer)
2. Irreversible and incapacitating central nervous system pathology
3. Irreversible and incapacitating cardiovascular system pathology
4. Systemic bleeding
5. Aortic dissection
6. Limited vascular access (severe peripheral arterial disease, extreme obesity, amputated limbs, among others)
7. Older age (increasing risk of death with increasing age)

*VA-ECMO, venoarterial extracorporeal membrane oxygenation; LVEF, left ventricular ejection fraction; SvO_2_, mixed venous oxygen saturation; ROSC, return of spontaneous circulation; VAD, ventricular assist device*.

* *Vasoactive-inotrope score (VIS): (Epinephrine dose + Norepinephrine dose) μg/kg/min × 100 + (Dopamine dose + Dobutamine dose) μg/kg/min*.

Patients will be withdrawn from the trial if: (1) the guardian makes such a request with no reasons; (2) the patient develops adverse events due to cardiopulmonary rehabilitation (e.g., rib fracture, limb fracture); and (3) the patient develops ECMO-related complications (e.g., bleeding, thromboembolism, severe infection) and is ever unsuitable for participating in the trial according to the point of view by clinicians.

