### Enrollment, Randomization, and Allocation

Eligible patients who meet the eligibility criteria and are provided with ECMO therapy in our Department of Emergency Medicine will be enrolled in the CaRe-ECMO trial. Their guardians will receive a detailed explanation of trial purpose and procedures. The patients will have a same chance to be randomly assigned to the CaRe-ECMO group or the control group. They also will be informed that they have the right to withdraw from the trial at any time of the trial period.

Simple randomization (1:1) will be applied using a computer generated random sequence, which will be independently administered and concealed by the Clinical Research Board from the School of Public Health of Nanjing Medical University (from here on called allocation center). Once a patient has been deemed eligible and the informed consent form has been signed, an independent trial assistant will register the participant, record her/his group allocation, and reveal the group allocation to those delivering the interventions (21). Figure 1 demonstrates the overview of the recruitment, randomization, and allocation based on the CONSORT principle.

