**Cardiovascular complications** **□ No □ Yes (If yes, then fill the following items)**
Date and time: ___ / ___ / ___, ___: ___
□ Cardiac arrest □ Newly developed myocardial infarction □ Heart failure □ Myocardium stunning (Ultrasound) □ Newly developed hypertension requiring vasodilator therapy □ Shock (□ Cardiogenic □ Hypovolemic □ Obstructive □ Distributive) □ North-south syndrome □ Tamponade (□ Blood □ Plasma □ Air)

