### Data Collection

Data in terms of rate of ready for ECMO weaning, rate of ECMO weaning, rate of mechanical ventilation weaning, all-cause mortality, and rate of major post-ECMO complications will be calculated throughout the index hospitalization and follow-up period (e.g., CaRe-ECMO days 7, 14, 30, and 90) according to daily evaluations recorded in the medical records. Outcomes, for instance ready for ECMO weaning, will be treated as time-to-event outcomes; therefore, date and timing of events will be also recorded to facilitate statistical analysis. Total length of ready for ECMO weaning, total length in hour of ECMO weaning, total length in day of mechanical ventilation, ECMO unit LOS, and total hospital LOS will be collected according to the medical records. CPC index, ADL score, and HRQoL score will be selectively collected among those successfully weaning of ECMO across discharge day (discharge from ECMO unit) and all follow-up time points (e.g., CaRe-ECMO days 30 and 90). In addition, diaphragmatic thickness and mobility will be evaluated with ultrasound (M-mode) every 3 days for determining the allocation of phrenic nerve and the efficacy of SEPNS. The detailed data collection schedule is given in Table 9.

**Table 9 T9:** Scheduled events and timeline of the CaRe-ECMO trial.

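### The post-ECMO complications endpoint is anchored to ECMO rather than to randomisation, and its recording sheet cannot reliably separate old events from new ones

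*Protocol article*

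**What the plan says.** All references are to the protocol article.

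- **Definition.** Secondary Outcomes, item 7: the endpoint "refers to rate of complications occurred after ECMO including but not limited to ECMO-related complications". The data come from the Complication Recording Sheet (Table 8).
- **Window.** Data Collection: the rate "will be calculated throughout the index hospitalization and follow-up period (e.g., CaRe-ECMO days 7, 14, 30, and 90".
- **Entry.** Eligibility and Withdrawal Criteria, criterion 4, requires patients "with stable condition and eligible for cardiopulmonary rehabilitation after 72 h of ECMO". Under Enrollment, Randomization, and Allocation, registration and allocation follow "Once a patient has been deemed eligible and the informed consent form has been signed".
- **Sheet.** The cardiovascular block of Table 8 includes "Newly developed myocardial infarction □ Heart failure □ Myocardium stunning (Ultrasound". Infarction and hypertension are restricted to new onset. Heart failure and shock in that block, and pulmonary infection and pulmonary edema in the respiratory block, are not. Each category has a single date and time field.
- **Analysis.** Statistical Methods: Cox regression and Kaplan–Meier curves up to CaRe-ECMO days 7, 14, 30 and 90. Table 9 schedules complications at those four times and not at t0.
- **Harms of the intervention.** One withdrawal reason is that "the patient develops adverse events due to cardiopulmonary rehabilitation (e.g., rib fracture, limb fracture". Table 8 has no box for either fracture.

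**The concern.** A randomised comparison of complications should start counting when the arms can begin to differ. Here the definition starts at ECMO and the window is the whole index hospitalisation, but the intervention cannot begin until at least 72 h later. Events in that interval have the same expected frequency in both arms and say nothing about rehabilitation.

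The sheet adds a second route to the same problem. A patient whose heart failure, shock or lung infection persists from entry can be ticked, because nothing asks whether the condition is new or worse. The effect is to pull the comparison towards no difference, and this would hide harm as readily as benefit. The two injuries that the plan itself attributes to rehabilitation have no place on the sheet, so it provides no like-for-like record of them in the two arms.

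**Working it through.** The plan states no rate, effect or power for this endpoint, so there is no figure to reproduce. The check has two parts.

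**1. The texts side by side**

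- *What the ECMO anchor means.* Table 8 includes oxygenator failure, pump failure and circuit change. These happen only on ECMO, so the anchor must be ECMO start and not ECMO removal.
- *Length of the interval.* Criterion 4 can be judged only after 72 h on ECMO, and allocation follows confirmed eligibility. Applied as written, at least 72 h of ECMO precede randomisation. (Table 9 heads its eligibility column with the day of ECMO. I assume criterion 4 governs.)
- *Is the interval excluded?* No sentence excludes it. Statistical Methods gives the end points of the curves and Table 9 gives the read-out times. Neither gives the time origin.
- *Would dates resolve it?* Not reliably. If two items in one category are ticked, one before and one after randomisation, a single date cannot describe both. The block for other complications puts extremity events, infection, bleeding and thrombosis under one date.
- *Are these findings expected at baseline?* Yes. In Table 10, the first examination after ECMO has radiology boxes for pulmonary infection, pneumothorax, pulmonary edema, atelectasis and cerebral hemorrhage. All five are also outcome boxes in Table 8.

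**2. Direction and illustrative size**

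Let q be the share of patients in each arm with a scored earlier event, and p the risk of a new event after randomisation. Assume that q is equal in the two arms and that p does not depend on the earlier event.

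- Observed risk = q + (1 − q)p
- Observed difference = (1 − q)(p_control − p_rehab)

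The shrinkage factor (1 − q) is exact under these assumptions, whatever the risks. For illustration, assume p = 50% and 35%, with the planned 183 per group and two-sided 5% alpha. Power for two proportions is Φ{[d − 1.96√(2p̄(1 − p̄)/n)] / √([p₁(1 − p₁) + p₂(1 − p₂)]/n)}, where p₁ and p₂ are the observed risks, d their difference and p̄ their mean.

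| q | Control | Rehabilitation | Difference (points) | Risk ratio | Power |
|---|---|---|---|---|---|
| 0 | 50.0% | 35.0% | 15.0 | 0.700 | 83.0% |
| 0.1 | 55.0% | 41.5% | 13.5 | 0.755 | 73.6% |
| 0.2 | 60.0% | 48.0% | 12.0 | 0.800 | 63.5% |
| 0.3 | 65.0% | 54.5% | 10.5 | 0.838 | 53.5% |
| 0.5 | 75.0% | 67.5% | 7.5 | 0.900 | 35.3% |

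Example, q = 0.3: control 0.3 + 0.7 × 0.50 = 0.65; rehabilitation 0.3 + 0.7 × 0.35 = 0.545.

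Assumed risks of 40% vs 25% and 60% vs 45% give the same pattern: power of 52.1% and 56.9% at q = 0.3, and 32.8% and 39.2% at q = 0.5. These figures describe cumulative proportions, not the planned Cox estimate.

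**The case against.** The strongest reply is that the analysis appears to run on CaRe-ECMO time. Trial Objectives counts CaRe-ECMO days from program initiation, event dates are to be recorded, Table 9 has no complication entry at t0, and the Daily Monitoring Sheet (Table 11) begins at CaRe-ECMO Day 1. On that axis an earlier event has negative time and would not ordinarily enter a Cox model. This is a fair reading and may be what is intended. It remains an inference, because the definition and the window wording point the other way, and one date per category can defeat it in practice.

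A reader might also infer that the disease that brought the patient to ECMO is itself scored, so that nearly every VA-ECMO patient starts with an event. The documents do not support this. An indication such as "Witnessed cardiopulmonary resuscitation for more than 10 min or intermittent ROSC but unable to maintain" comes before ECMO, and the definition excludes what began before ECMO. The arrest is a past event, and persisting shock is made less likely by the stability required at entry. What remains is that the sheet does not ask whether a persisting condition is new or worse. The overlap is also weaker for VV-ECMO, whose indications in Table 2 are gas-exchange and airway criteria.

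Nor does the text say that every tick counts as major. It says only that information is collected on Table 8, and counting rules may sit in a document not shown. The open-ended list and the two cerebral hemorrhage boxes change little for a patient-level or time-to-first-event outcome.

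On fractures, withdrawal reasons and reasons for stopping a session are recorded, and safety is reviewed by the monitoring committee. It is therefore too strong to say that fractures will never be compared. But session records arise from rehabilitation sessions, which controls do not receive.

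**Conclusion.** The concern holds as a fault of anchor and data capture in one secondary endpoint. The written definition and window admit at least 72 h of complications before randomisation. Nothing stated excludes them, unqualified boxes allow persisting conditions to be ticked, and the date fields may not allow later repair. If such events are counted in both arms, the risk difference shrinks by (1 − q). That direction rests on q being equal between arms, as randomisation makes it in expectation. The size cannot be known, since the documents give neither q nor complication rates, and the table above is illustration only. It is not established that earlier events will be scored, only that the wording permits it. The primary outcome is not affected.

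**What to change.** - Define the endpoint as the first listed complication that is new or worsened after randomisation, and state randomisation as the time origin. It is a moment that exists in both arms.
- Complete Table 8 once at t0, or use the equivalent Table 10 entries where they exist, and do not count items already present.
- Give each ticked item its own date and time in place of one field per category.
- Add rib fracture, limb fracture and other rehabilitation-related events to Table 8, recorded in both arms with presence at t0. Resuscitation before entry may already have caused rib fractures.

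The cost is a revised definition, a revised sheet and one extra completion of an existing form. Fewer events will be counted, but those that remain are ones the intervention could have influenced. Table 1 gives recruitment as not yet started, so if that still holds the form can be changed before any data are collected on it.
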